**Table 2 T2:**

Sequences and references for primers used.

To determine the number of plasmid copies/ μl, necessary to assemble the qPCR curve, it will be estimated that 1 μg of 100 bp of DNA would be equivalent to 9x10^11^ plasmids. These will then be serially diluted, and the curve will comprise 10 to 10^8^ plasmids, which will then be compared to the DNA of the analyzed samples. The number of *Universal Bacteria* will be calculated assuming 1 copy of the 16S rRNA gene/ chromosome.^[37]^ As a negative control sterile Milli-Q water will be added instead of DNA to the template.

Quantitative analysis will be performed by comparing the results obtained with the samples to the data obtained with the standard curve. For the quantification of *Universal Bacteria* 16S rRNA in saliva and biofilm samples, species-specific primers (5 ’CCATGAAGTCGGAATCGCTAG 3” and 5’ GCTTGACGGGCGGTGT 3’) will be used.^[37]^ The reaction will be realized with a total volume of 10 μL containing 5 μL of SYBR Green, 2 μL of sample and 200 μM of each primer for 16S rRNA. Cyclization will be performed: 95°C / 10 min holding, 40 cycles at 95°C / 15 s, 60°C / 1 min, melting curve 95° C / 15 s, 60°C / 1 min (+0.6°C collection) and 95^o^C / 15 s. Only those reactions in which the efficiency was 100% (+ or - 10) R^2^ near to 1 will be considered.

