### Statistical analysis

2.15

Statistical analysis will be performed using only the data obtained from patients who have completed the study. If the sample is normally distributed, Student's T test will be used to compare the means of the continuous and dependent variables. If the distribution is not normal, the Mann-Whitney test will be used. Data will be presented by their means ± SD and the p value will be set at 0.05. All tests will be performed using GraphPad Prism 5 (GraphPad Software, San Diego, USA). The significance level will be set at *p* < 0.05.

Spreadsheets with the survey data will be stored in their own space during the survey. To avoid duplicate data entry, only one researcher will be responsible for entering the data into the spreadsheets for further statistical analysis. The responsible is [name].

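### In the qPCR calibration, the DNA length (100 bp) and the copy number (9x10^11 per μg) disagree by a factor of about ten and must be reconciled

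*Protocol article*

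**What the plan says.** Section 2.14.5.4 (Real-time PCR), in the text under Table 2, gives one mass-to-copies conversion and says what it is for: "To determine the number of plasmid copies/ μl, necessary to assemble the qPCR curve". The conversion is that 1 μg "of 100 bp of DNA would be equivalent to 9x10^11^ plasmids". The standards are then serially diluted, so that "the curve will comprise 10 to 10^8^ plasmids, which will then be compared to the DNA of the analyzed samples". Sample quantities come from that curve: "Quantitative analysis will be performed by comparing the results obtained with the samples to the data obtained with the standard curve". Copies become bacteria by "assuming 1 copy of the 16S rRNA gene/ chromosome". No plasmid length, insert length or other calibration is given.

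Section 2.13 lists the universal bacterial count, in crevicular fluid and saliva at baseline, 7 and 21 days, among the secondary variables; the primary variable is the gingival index (GI). Section 2.15 plans a Student's t-test or a Mann-Whitney test, and its general reporting rule is "Data will be presented by their means" with SDs.

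**The concern.** The number of molecules in a given mass of DNA is fixed by the length of the molecule. A length and a copy number stated as a pair can therefore be checked against each other, and this pair fails by about one power of ten.

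The pair matters because it is the only calibration described between DNA mass and the counts that the trial will report. A wrong conversion would mislabel every standard by the same factor, and every sample read from the curve would inherit it. What is at stake is the absolute scale of a secondary variable: the published counts, their means and SDs, and any raw difference between arms. The comparison between arms is not at stake.

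**Working it through.** **Inputs from the protocol (section 2.14.5.4, text under Table 2):** mass 1 μg; length 100 bp; stated copies 9x10^11; curve range 10 to 10^8.

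**Assumed, not given in the document:** Avogadro's number 6.022x10^23 per mol; molar mass of double-stranded DNA 650 to 660 g/mol per bp, with 600 to 680 as a wide range.

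**Formula:** copies per μg = 10^-6 x 6.022x10^23 / (length in bp x mass per bp).

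**1. Trying to reproduce the stated figure at 100 bp.**

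| g/mol per bp | Calculation | Copies per μg | Ratio to 9x10^11 |
|---|---|---|---|
| 600 | 6.022x10^17 / 60,000 | 1.00x10^13 | 11.2 |
| 650 | 6.022x10^17 / 65,000 | 9.26x10^12 | 10.3 |
| 660 | 6.022x10^17 / 66,000 | 9.12x10^12 | 10.1 |
| 680 | 6.022x10^17 / 68,000 | 8.86x10^12 | 9.8 |

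The stated figure is not reproduced. The gap is 9.8- to 11.2-fold, and no value in the range of base-pair masses closes it. Reading the DNA as single-stranded (about 304 to 330 g/mol per nucleotide) gives 1.8x10^13 to 2.0x10^13, which is further away.

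**2. The length that the stated figure fits.** Length = 6.022x10^17 / (9x10^11 x mass per bp). This gives 1,029 bp at 650 g/mol and 1,014 bp at 660 g/mol (984 to 1,115 bp over 680 to 600 g/mol). In the other direction, 1,000 bp gives 9.26x10^11 at 650 and 9.12x10^11 at 660. One power of ten has been lost, either in the length or in the exponent.

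**3. Consequence if the pair is used as written on a 100 bp standard.** A tube labelled N copies holds about 10N. The nominal end points become 10 x 10.3, about 10^2, and 10^8 x 10.3, about 10^9. Sample counts read from the curve are about tenfold too low, a shift of about 1.0 on the log10 scale.

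**4. Consequence if the standard is about 1,000 bp.** The conversion is then right to within a few per cent, and the counts and the curve range stand. Only the printed length is wrong.

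**5. Effect on the comparison of arms.** Suppose every count is multiplied by the same constant k. In the t statistic, the mean difference and its standard error are both multiplied by k, so k cancels. Ranks do not change, so the Mann-Whitney test does not change. On the log scale k adds the same constant to both arms and drops out of differences. As a check, multiplying a simulated data set of 17 v 17 by 10 left the p-values unchanged: 0.650 for the t-test on raw counts, 0.0275 for Mann-Whitney and 0.0429 for the t-test on log10 counts. A constant factor also shifts only the intercept of the standard curve, so the slope and the efficiency criterion in the same section are untouched.

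**The case against.** The strongest reply is that this is probably a typing slip in a laboratory detail. The stated number fits about 1,000 bp closely, so a dropped zero in the length explains the mismatch at least as well as a wrong exponent. In that case nothing in the laboratory is wrong. The bacterial count is secondary, the planned tests are insensitive to scale, the document plans no comparison of absolute counts with other studies, and the counts are already nominal because one gene copy per chromosome is assumed.

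Most of this stands. It limits the consequence and rules out three stronger readings that a reader might infer.

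- **That every reported count is wrong.** The document shows a mismatched pair of figures, not the length of the DNA that will be diluted. The counts are wrong only if the conversion is applied as written to a standard of a length it does not fit.
- **That the error is known to run in the opposite direction because the text speaks of plasmids.** For an assumed whole plasmid of 3,000 to 4,000 bp, the formula at 650 to 660 g/mol gives 2.3x10^11 to 3.1x10^11 copies per μg, and an unscaled 9x10^11 would make counts about 3 to 4 times too high. The document gives no plasmid length, so this is a reason to ask for the length and not a finding about direction.
- **That 9x10^11 should simply be replaced.** If the length is the slip, changing the exponent would create the tenfold error.

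The reply does not remove the mismatch. The protocol chose to fix this constant, the two halves cannot both be right, and nothing elsewhere in the document corrects them.

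**Conclusion.** The point holds as an internal inconsistency. The length and the copy number used to build the qPCR standard curve disagree by a factor of about ten (9.8 to 11.2 over 600 to 680 g/mol per bp, double-stranded DNA assumed).

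The consequence is conditional. Used as written on a 100 bp standard, the conversion makes absolute 16S rRNA counts and their means, SDs and raw differences about tenfold too low. With a standard of about 1,000 bp, only the text needs correcting. The document does not say which applies.

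Between-arm p-values, fold changes and log differences are unaffected in either case, provided that the same conversion is used for all samples. The primary variable, GI, does not depend on the assay. The correction is worth making because this is the only calibration described for a listed outcome, but it does not threaten the trial's inference.

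**What to change.** Before any counts are calculated:

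1. State the total length of the standard that is actually diluted: vector plus insert if it is a whole plasmid, or the fragment length if it is an amplicon.
2. Compute copies per μg as 10^-6 x 6.022x10^23 / (length in bp x mass per bp), and state the mass per bp used.
3. Correct whichever of the two printed figures, 100 bp or 9x10^11, proves wrong. Do not change the exponent before the length has been confirmed.
4. Restate the curve range of 10 to 10^8 only if the copy number changes.

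The cost is one check of the laboratory record and one corrected figure in the text. No new assay, sample or change of design is needed. If counts have already been calculated with a wrong conversion, one multiplication puts them right.

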##### Analysis of salivary cytokine and crevicular fluid profile

2.14.5.5

Determination of the levels of the inflammatory markers TNF-α, IL1-β, IL-6 and IL-8 and IL-10 in the salivary and crevicular fluid will be performed via ELISA, using commercial kits (PeproTech Inc., Rocky Hill, NJ, USA) according to the manufacturer's instructions.

A flowchart is presented for an overview of the study (Fig. 1).

**Figure 1 F1:**
[figure not shown]
Flowchart. REC = Research Ethics Committee, ICF = Informed Consent Form, PSR = Periodontal Screening and Recording, GI = gingival index, OHIP-14 = Oral Health Impact Profile Questionnaire, PII = plaque index, PD = probing depth, PDT = photodynamic therapy, SSRP = scaling and root planning.

### Statistical analysis

2.15

Statistical analysis will be performed using only the data obtained from patients who have completed the study. If the sample is normally distributed, Student's T test will be used to compare the means of the continuous and dependent variables. If the distribution is not normal, the Mann-Whitney test will be used. Data will be presented by their means ± SD and the p value will be set at 0.05. All tests will be performed using GraphPad Prism 5 (GraphPad Software, San Diego, USA). The significance level will be set at *p* < 0.05.

Spreadsheets with the survey data will be stored in their own space during the survey. To avoid duplicate data entry, only one researcher will be responsible for entering the data into the spreadsheets for further statistical analysis. The responsible is [name].

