### Inclusion / exclusion criteria

2.3

To be included: healthy participants (negative medical history), of both genders, aged 10 to 30 years, with gingivitis induced by dental biofilm, predisposed by the use of a fixed orthodontic appliance, according to the classification of 2018.^[33]^

To be excluded: participants with maxillary and mandibular deformities, periodontitis, oral lesions and who have used antibiotics for less than 3 months, those who have used non-steroidal anti-inflammatory drugs and continuous corticosteroid therapy^[1]^ for less than 3 months, as well as those who have been using a mouthwash in the past 3 months. Participants who have modifying factors for periodontal disease, such as diabetics, immunosuppressive smokers (cyclosporine), anticonvulsants (phenytoin), calcium channel blockers (nifedipine) and pregnant and lactating women as well as those who are HIV positive, or have Hepatitis B or C. Patients who require prophylactic antibiotic therapy for periodontal treatment who have had periodontal treatment in the last 6 months. Patients who have non-biofilm-induced gum disease.^[33]^ Patients who for some reason during the study have to initiate the use of the medicines and mouthwashes mentioned above or acquire a disease that is a modifying factor for periodontal disease or become pregnant. Patients who do not wish to remain part of the study may drop out whenever they wish.

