### Randomization

2.5

To randomly distribute the participants into the experimental groups, a 40-lot draw will be made using the Microsoft Excel program, version 2017. The distribution of groups will be identical (1: 1) for the two groups. The distribution will be done in a blocking fashion (8 groups of 5 patients). Opaque envelopes will be identified with sequential numbers (1 to 40) and there will be information about the corresponding experimental group in the order obtained in the draw. The envelopes will be sealed and will remain sealed in numerical order until the start of the periodontal treatments. The drawing and preparation of the envelopes will be performed by a person not involved in the study. Immediately prior to periodontal treatment the investigator responsible for treatment will open 1 envelope (without changing the numerical sequence) and perform the indicated procedure. Three additional patients will be included in each group in view of the dropout predicted in any clinical study (considering a dropout of 20%).

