### Oral hygiene guidance (OHG)

2.11

Immediately prior to treatment all participants will receive OHG: BASS brushing technique, specifications for toothbrush (soft bristles, only two rows for hygiene below and above brackets, narrow, rectangular head), interdental brush (0.05 mm) and dental floss (with wax attached to the thread).

To ensure that participants are adhering to the guidelines, they will be asked to bring their brushes and floss to check if the brushing technique is being performed correctly.

At all meetings the participant will be questioned about the use of mouthwashes as it is prohibited during the study. If use is reported, the participant will be excluded from the study.

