### Study variables

2.13

The primary study variable will be

GI as determined using a periodontal probe at baseline (T_0_), 7 (T_1_) and 21 (T_2_) days after treatment.

The secondary variables of the study will be:

Clinical PD at baseline (T_0_), 7 (T_1_) and 21 (T_2_) days after treatment;Visible PI at baseline (T_0_), 7 (T_1_) and 21 (T_2_) days after treatment;GI at baseline (T_0_), 7 (T_1_) and 21 (T_2_) days after treatment.Oral health-related quality of life (OHRQoL) will be assessed using the OHIP-14 questionnaire at baseline (T_0_) and 21 (T_2_) days after treatment;Evaluation of cytokines IL-6, IL-1β, IL-8, TNF-α and IL-10, by ELISA method, in non-stimulated saliva and crevicular fluid at baseline (T_0_), 7 (T_1_) and 21 (T_2_) days after treatment;Microbiological analysis by means of the *Universal bacteria* count (16S rRNA gene) present in crevicular fluid (sites with hyperplasia), and non-stimulated saliva at baseline (T_0_), 7 (T_1_) and 21 (T_2_) days after treatment.

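### The only planned analysis is of completers, and patients who start mouthwash or listed medicines after randomisation are removed; these exclusions may relate to the primary outcome, and no planned analysis would show it

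*Protocol article*

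**What the plan says.** The analysis population is fixed in section 2.15 of the protocol article: "Statistical analysis will be performed using only the data obtained from patients who have completed the study". The article names no other analysis set.

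Two other sections remove patients during follow-up:

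- Section 2.11 (Oral hygiene guidance): "At all meetings the participant will be questioned about the use of mouthwashes as it is prohibited during the study". The consequence follows directly: "If use is reported, the participant will be excluded from the study".
- Section 2.3 (Inclusion / exclusion criteria) lists among those to be excluded "Patients who for some reason during the study have to initiate the use of the medicines and mouthwashes mentioned above", and in the same sentence those who "acquire a disease that is a modifying factor for periodontal disease or become pregnant". The medicines meant are antibiotics and, in the article's words, "those who have used non-steroidal anti-inflammatory drugs and continuous corticosteroid therapy".

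Section 2.5 gives the time of randomisation: "Immediately prior to periodontal treatment the investigator responsible for treatment will open 1 envelope". Section 2.13 defines the primary variable: "GI as determined using a periodontal probe at baseline (T_0_), 7 (T_1_) and 21 (T_2_) days after treatment". Any exclusion found at day 7 or day 21 therefore comes after randomisation.

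**The concern.** Randomisation makes the two groups comparable as allocated. Removing patients for something that happens afterwards keeps that comparability only if the removal is unrelated to outcome, or is equally selective in both arms.

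Neither condition can be taken for granted here. Section 2.2 lists bleeding, pain and halitosis among the relevant complaints, and the Discussion says that gingival inflammation may cause pain. A patient whose gums have not improved may be more likely to reach for a mouthwash or an anti-inflammatory. The primary variable is the percentage of sites that bleed, so such a patient may also be one with a poor GI. If treatment response differs between arms, so may the exclusions.

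The completer rule adds a second loss. A patient examined at day 7 and excluded or lost later contributes nothing, although the day-7 GI was measured. Because the completer analysis is the only one, no result in the report would show whether any of this mattered.

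**Working it through.** **1. Is this fixed by the article or left open?** Section 2.15 limits all statistical analysis to completers. Section 2.11 says that a patient reporting mouthwash leaves the study, so that patient cannot be a completer. Section 2.3 does the same for listed medicines, modifying disease and pregnancy. Randomisation is immediately before the single treatment session (sections 2.5 and 2.12.1). Read together, these are stated post-randomisation exclusions from the only analysis, not detail left to an analysis plan that is not shown.

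**2. The plan's own figures.** Sections 2.1 and 2.5 give 17 + 3 = 20 per group, 40 in all, with 20% drop-out expected. The extra patients restore numbers but not comparability. The drop-out figure is general; none of it is attributed to mouthwash or medicines.

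**3. Bias formula.** Let arm *i* lose a fraction *p* of its patients, who would have ended *δ* SD worse on GI than those retained. The retained mean is then better than the full-arm mean by *p × δ*, and the completer difference is off by

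shift = *p*₁*δ*₁ − *p*₂*δ*₂,

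where 1 is control (G1) and 2 is PDT (G2). A positive value moves the comparison against PDT.

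**4. Illustration (*p* and *δ* are assumptions).**

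- One arm alone loses 4 of 20, *δ* = 1: 4/20 × 1 = 0.20 SD.
- One arm alone loses 4 of 20, *δ* = 0.5: 4/20 × 0.5 = 0.10 SD.
- Both arms lose 4 of 20 with the same *δ*: 0.20 − 0.20 = 0.

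**5. Stress cases (also assumptions; no true effect).** Suppose the excluded patients are exactly the worst fraction *q* of a normal distribution. The mean of those left is −φ(*c*)/(1 − *q*), with *c* the (1 − *q*) quantile: −0.350 for *q* = 0.20, −0.274 for 0.15, −0.109 for 0.05.

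| Excluded G1 / G2 | Shift (SD) |
|---|---|
| 20% / 20% | 0 |
| 15% / 15% | 0 |
| 15% / 5% | 0.17 |
| 20% / 5% | 0.24 |
| 20% / 0% | 0.35 |

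If exclusion is only partly tied to GI (correlation 0.3 to 0.5), the three unequal cases shrink in proportion, from 0.3 × 0.166 = 0.05 SD to 0.5 × 0.35 = 0.18 SD.

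**6. Scale.** With 17 per arm the standard error of a difference in means is √(2/17) = 0.34 SD. A shift of 0.10 to 0.20 SD is about 0.3 to 0.6 of that.

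**7. Day-7 data.** If the full 20% of 40 were lost, and all after day 7, 0.20 × 40 = 8 patients' day-7 values would be discarded. This is an upper bound for that drop-out rate, because a patient lost before day 7 has no such value.

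**The case against.** The best defence is that removal has a rationale. Mouthwash, antibiotics and anti-inflammatories can themselves change GI, bacterial counts and cytokines, and the same agents are exclusions at entry. That stands as a reason to report a compliant set. It does not justify making that set the only analysis.

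The second defence is blinding. Section 2.6 blinds the patient, the data collector, the microbiologist and the statistician, and the rules are the same in both arms. If PDT has no effect, persisting bleeding should drive exclusions about equally and the expected bias is nil. If PDT works, control would lose more of its worst patients and the difference would shrink. This largely stands: the mechanism described here is mainly conservative, and the unequal stress cases with no true effect would need some other cause or chance.

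Several stronger readings are tempting but unsupported:

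- A reader might infer that patients take these products because their gums still bleed. Section 2.3 gives no reason, and people aged 10 to 30 may take antibiotics or anti-inflammatories for unrelated causes. Exclusion *may* depend on outcome; the documents do not show that it does.
- A reader might set 0.20 SD against the stated effect size of 0.40 and call it half the planned effect. Section 2.1 sets 0.40 for bacterial count in crevicular fluid, and its type is not given. It is no benchmark for GI.
- A reader might infer that the completer analysis favours PDT. The documents offer no mechanism for that direction.

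**Conclusion.** The point holds and should be fixed. That completers are the sole analysis set, and that randomised patients are removed for events after allocation, is explicit in the text. What cannot be said is how large the bias is, or in which direction: the documents give no exclusion rate and no reasons. It is zero under equal and equally selective exclusion, and towards no difference if PDT works and control loses more of its worst patients. The 0.10 to 0.20 SD illustration rests on the assumption that one arm alone loses 4 of 20 patients who would have ended 0.5 to 1 SD worse. The firm consequences are that the comparison is no longer of the groups as randomised, that measured day-7 data are thrown away, and that nothing planned would expose a problem.

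**What to change.** In section 2.15, make the primary analysis all randomised patients in their allocated groups, using every available T1 and T2 value. A repeated-measures model with baseline GI is one suitable way to do this. Report the completer or compliant set as a sensitivity analysis, with the number and reasons for exclusion by arm.

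In sections 2.3 and 2.11, separate the restriction from its consequence for the data. The restriction on mouthwash and medicines can stay as it is. A patient who reports such use should still have the scheduled day-7 and day-21 data collected, with the use recorded, unless the patient withdraws.

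The cost is a change of wording and completion of visits that are already scheduled. The downside is that some off-protocol product use is averaged into both arms; the sensitivity analysis shows how much that matters. The change should be made before follow-up is complete, because data not collected after an exclusion cannot be recovered.

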## Abstract

It is known that the presence of orthodontic brackets predisposes for a change in the biofilm, facilitating the development of gingivits. The sites are difficult to access with a toothbrush and periodontal curette, worsening inflammation, in addition, a gingival hyperplasia is associated with poor hygiene. The objective of this study is to evaluate the impact of photodinamyc therapy (PDT) as an adjuvant treatment, considering clinical immunoregulatory and microbiological parameters. This randomized, controlled, double-blind clinical study will include 34 patients, both genders, having used fixed appliance for more than 12 months, with gingivitis. Participants will be divided into two groups: G1 (n = 17)- Scaling and Root Planing + PDT placebo and G2 (n = 17)- Scaling and Root Planing + PDT. In G2 the following dosimetric parameters will be used: methylene blue 0.005%, λ= 660 nanometers (nm), 9 Joules (J) per site, irradiance= 3.5Watts (W)/ centimeters (cm), radiant exposure= 318J/cm^2^. All participants will receive oral hygiene guidance prior the curetes scaling. The clinical periodontal data to be analyzed are plaque index, gingival index and probing depth. Crevicular fluid, from 4 pre-determined sites and saliva, will be collected and analysed for IL-6, IL-1β, IL-8, TNF-α and IL-10 cytokines using ELISA (Enzyme immunoabsorption assay) method. Total *Bacteria* count will also be performed, by qPCR and *Universal16SrRNA* gene. All analysis will be realized using in the baseline (T_0_), 7 (T_1_) and 21 (T_2_) days after treatment. Oral health-related quality of life will be assessed using the OHIP-14 questionnaire at times T_0_ and T_2_. If sample distribution is normal, the Student T-test will be applied if it is not normal, the Mann-Whitney test will be used. The data will be presented in terms of ± PD and The significance level will be set at p < 0.05. Our results may improve quality of life and add data to establish a therapeutic alternative for gingivitis during the orthodontic treatment. Registration: clinicaltrials.gov NCT04037709. https://clinicaltrials.gov/ct2/show/NCT04037709 - Registered in July 2019.

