#### Analysis of oral health-related quality of life - OHIP-14

2.14.4

The OHIP-14 questionnaire is a simplified form of the original OHIP-49 questionnaire and will be used to assess the impact of oral health on the quality of life of the research participants. The OHIP-14 is used to measure perceived needs; evaluating the impact of oral changes on Oral health-related quality of life. The patient responds to 14 questions by assigning the values:

0 (never),1 (almost never),(sometimes),(most of the time),(always) to his or her answers.

In this study it will be evaluated the OHIP-14 using the additive method and domain evaluation. In the additive method, when the value is greater than 1, one can consider the presence of a negative impact on the life of the individual. OHIP-14 will be assessed at baseline and after 3 weeks for all subjects.

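### The plan fixes an unadjusted two-sample test picked by a normality check and gives the baseline value of each outcome no stated role, which loses precision at 17 per arm

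*Protocol article*

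**What the plan says.** The Statistical analysis section states the method in two sentences. For normally distributed data, Student's "T test will be used to compare the means of the continuous and dependent variables. If the distribution is not normal, the Mann-Whitney test" is applied instead. The Abstract gives the same rule: "If sample distribution is normal, the Student T-test will be applied if it is not normal, the Mann-Whitney test will be used". Neither place says how normality will be judged, or whether the choice is made per outcome, per visit or per arm. Results are summarised in one way whichever test is used: "Data will be presented by their means ± SD".

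Baseline is collected throughout. The primary variable in the Study variables section is "GI as determined using a periodontal probe at baseline (T_0_), 7 (T_1_) and 21 (T_2_) days after treatment", with no single visit picked out. The Abstract says of the clinical, cytokine and bacterial measures: "All analysis will be realized using in the baseline (T_0_), 7 (T_1_) and 21 (T_2_) days after treatment". For quality of life, "OHIP-14 will be assessed at baseline and after 3 weeks for all subjects".

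The opening of Materials and methods says that clinical measures will be compared after 7 and 21 days to look for improvement. It does not say how the baseline value enters that comparison.

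**The concern.** The article names its tests itself, and does so twice, so this is not a detail left to a fuller document. Both tests compare two independent samples and take no covariate. The baseline reading of the same outcome is usually the best available predictor of its follow-up reading. A test that leaves it out keeps variation between patients in the error term that could have been removed at no cost. With 17 completers per arm, that precision matters.

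The normality switch adds a second difficulty. The t-test compares means and Mann-Whitney compares ranks, so the question answered would depend on the observed sample. Means with standard deviations would be reported even where the test was a rank test.

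**Working it through.** **Inputs**
- 17 per arm, 34 in total (Calculation of sample size; Experimental design).
- Significance level 0.05 (Statistical analysis). Two-sided is assumed, as the article does not say.
- 80% power is assumed as the yardstick for the detectable difference.
- Baseline-to-follow-up correlation ρ is not in the article. I assume 0.3, 0.5 and 0.7.

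**The plan's own figure.** The article gives no figure for the precision of the comparison. Its 34 is taken as given here, although it does not follow from a standardised effect d of 0.40: 2 × (1.96 + 0.84)² / 0.40² = 98.1, so 99 per group or 198 in total. That is a separate point.

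**Gain from baseline adjustment**
1. Residual variance relative to the follow-up-only test is 1 − ρ².
2. Estimating the covariate inflates the expected variance by 1 + 1/(2n − 4). With n = 17 this is 1 + 1/30 = 1.033.
3. The equivalent unadjusted sample size is 34 divided by the net factor.
4. The detectable d at 80% power is 0.99 unadjusted (t-test, 17 per arm). Multiplying 0.991 by √(1 − ρ²), and then by √1.033 = 1.017, gives the last two rows.

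| | ρ = 0.3 | ρ = 0.5 | ρ = 0.7 |
|---|---|---|---|
| 1 − ρ² | 0.91 | 0.75 | 0.51 |
| × 1.033 (net) | 0.940 | 0.775 | 0.527 |
| Net variance cut | 6% | 22% | 47% |
| 34 / net factor | 36 | 44 | 65 |
| Detectable d, before covariate cost | 0.95 | 0.86 | 0.71 |
| Detectable d, after covariate cost | 0.96 | 0.87 | 0.72 |

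The net factor equals 1 when ρ² = 1/31, that is ρ = 0.18. Below that, adjustment loses slightly.

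**If change from T0 is what will be tested.** With equal variances at the two visits, the variance relative to follow-up-only is 2(1 − ρ) = 1.40, 1.00 and 0.60. This is worse than follow-up-only for ρ below 0.5. The excess over ANCOVA, before the covariate cost, is 2(1 − ρ) − (1 − ρ²) = (1 − ρ)², which is never negative. After that cost the comparison is 1.40, 1.00 and 0.60 against 0.940, 0.775 and 0.527.

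**The normality switch.** This was simulated with Shapiro-Wilk in each arm (an assumption, as no normality test is named), 17 per arm and 8000 trials per case. Type I error was 0.050 for normal data, 0.060 for lognormal data with log-scale SD 0.5, and 0.048 for lognormal data with log-scale SD 1. In the middle case the t-test was chosen in 31% of trials and Mann-Whitney in the rest.

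**The case against.** **Baseline may not be ignored.** The article never says whether follow-up values or changes from T0 are tested, and a two-sample test can be run on changes. That is correct, so a reader should not infer that T0 will certainly go unused. What stands is that it has no stated role, and that change scores would still be no better than ANCOVA apart from the small covariate cost.

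**The unadjusted test is valid.** A reader might infer that chance baseline imbalance biases the result. It does not: the unadjusted standard error already allows for it. The loss is precision only.

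**The gain may be small.** Entry requires GI above 10%, and every patient receives scaling and hygiene guidance. Both could weaken the correlation for GI. This stands. At ρ = 0.3 the net gain is only about 6%.

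**The switch does little measurable harm.** A reader might infer serious error inflation or an unreliable procedure. The simulated type I error of 0.048 to 0.060 does not support that. What remains is prespecification and the change in the question answered.

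**Skewness is not documented.** A reader might take the qPCR standard curve of 10 to 10⁸ plasmids as evidence of skewed counts. It is the assay's calibration range and says nothing about the spread between patients.

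**The 0.40 effect is for another outcome.** A reader might scale the loss against it. The article sets it for bacterial amount in crevicular fluid and gives no effect size for GI.

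**A linear model is not ideal for every outcome.** GI is a bounded percentage and OHIP-14 an ordinal sum. This is fair, and is a reason to keep a rank-based sensitivity analysis.

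**Conclusion.** The point holds as one of avoidable inefficiency. The article fixes an unadjusted test, selected from the data, and leaves the baseline value of every outcome without a stated role. The net variance saving from adjustment is about 6%, 22% or 47% at assumed correlations of 0.3, 0.5 or 0.7. The direction is secure for any correlation above about 0.18. The size is not, because the article gives no correlation. The comparison with follow-up-only testing also assumes that changes are not what will be tested.

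Adjustment does not rescue the trial's power. At a standardised effect of 0.40, power with 17 per arm rises from 20% to 22%, 26% or 35%. Reaching 80% would still need 74 per group at ρ = 0.5 or 51 at ρ = 0.7. The sample size therefore has to be dealt with separately. The analysis should be changed because the gain is nearly free, not because the planned test is wrong.

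**What to change.** Replace the test rule in the Statistical analysis section and the Abstract with the following:
- **Primary analysis.** Name one visit in advance, for example day 21. Analyse GI at that visit by ANCOVA with group and baseline GI, and report the adjusted difference with its 95% confidence interval. A repeated-measures model over T1 and T2 with baseline as covariate, read at the named visit, would also serve.
- **Other outcomes.** Adjust each for its own baseline value. Set the scale for bacterial counts and cytokines in advance, for example log10 with results as geometric mean ratios.
- **Normality switch.** Remove it, and keep Mann-Whitney as a stated sensitivity analysis.
- **Summaries.** Match the descriptive statistics to the scale analysed.

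The cost is one degree of freedom, revised wording and software that fits a linear model with a covariate. No extra patients, visits or samples are needed.
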